#### Qualitative assessments

Mentees and mentors will also complete a qualitative online reflection exercise (informed by Broom et al. [34]; see Additional file 1: Appendix E) prior to commencing the program (at baseline) and at 3 months (refer to Fig. 1) to determine the efficacy and feasibility of the program. At the completion of the program (i.e. 6 months), mentees and mentors will complete a final online reflection exercise and take part in semi-structured qualitative interviews.

The aims of this aspect of the study are to investigate the experience of mentors and mentees and to identify positive and negative aspects of the experience and factors related to these positive and negative experiences. Using the six-stage approach described by Braun and Clarke [35], thematic analysis will be undertaken to identify key themes in the data gathered through online reflection exercises and qualitative interviews. Data familiarisation (stage 1) will be effected through processes of transcription (of interviews) and close reading of all qualitative data. Preliminary coding (stage 2) identifies themes and patterns discussed by mentees; this process also supports the iterative refinement of the interview schedule (discussed below). The more systematic stage 3 involves the structured identification of recurrent themes, which is followed by a process of refining the codes so that redundant codes can be removed from our analysis (stage 4). A process of cross-checking ensures that the findings of the study are coherent and rigorous. The main themes identified following these processes (stage 5) will form the foundation of the research findings, which are then disseminated (stage 6).

##### Online reflection exercises

Mentees and mentors will be emailed a link to a secure online survey at the time points outlined in Fig. 1 and will have access to this link for 10 days. Online reflection exercises completed by mentors and mentees will allow for detailed exploration of the most important, empirically relevant themes associated with participating in a mentoring program.

Online reflection exercises will cover areas A–C in Additional file 1: Appendix F, with language modified slightly to reflect the current stage of the program. For example, questions asked at baseline will be future-oriented (‘Why did you decide to participate in the mentoring program?’ or ‘What might be some of the positive aspects of participating in this program?’). For mentors, these questions will also include reflections on their experience of the recruitment and training process. Questions asked while the program is ongoing will be based on current experiences (for example, ‘What has been your experience of participating in the mentoring program so far?’). Questions asked at completion of the program will ask respondents to reflect on their experiences of the program as a whole.

##### Qualitative interviews and feasibility

Given the limitations of the existing literature, the explorative nature and the qualitative research methodology of the current investigation, a broad semi-structured interview schedule will be used on completion of the program. This will be revised iteratively throughout the study to enable exploration of new themes raised by participants (mentors and mentees) and enable detailed exploration of the most important and relevant themes associated with participating in this program. The qualitative interviews will also cover areas A–C (see Additional file 1: Appendix F). The number of mentoring sessions completed and the participants’ capability to complete the mentoring sessions will also be assessed through the qualitative interviews.

Feasibility of the program will be guided by the CONSORT statement regarding assessing feasibility of trials [36]. Specifically, feasibility will be measured in terms of achieving sufficient numbers of participants signing up, participating and being retained in the program through the qualitative interview and records kept by mentors regarding program participation. The study will be deemed feasible if 80% of participants are able to complete the program and the target sample size is achieved within 2 years. Feasibility will also be measured in terms of tolerance and acceptance of the intervention, that the intervention can be delivered as per the protocol and identifying any adverse events related to the study through the qualitative interview and the participant feedback questionnaires. Any serious adverse events will result in the intervention not continuing to an RCT.

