Mentors will complete an online questionnaire at the conclusion of each mentoring session to document progress and monitor safety considerations (see Additional file 1: Appendix C). This will be reviewed by the EDV project coordinator and allows timely follow-up with any mentee or mentor needing individual support.

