### Program evaluation

Informed consent will be sought by one of the research staff from all mentees and mentors to take part in the evaluation of the program, which includes quantitative and qualitative measures. Quantitative data will be collected in a re-identifiable form at baseline (beginning of the program), at 3-month (mid-program) and 6-month (end-of-program) time points, and at 12-month follow-up for both mentees and mentors (see Fig. 1). Qualitative assessments will involve online reflection exercises completed at baseline, mid-program and end-of-program time points, and a qualitative interview undertaken upon completion of the program for both mentees and mentors. In addition, attrition will be tracked by the researchers through records of sessions that the mentors keep.

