#### Quantitative assessments

The following quantitative measures will be collected at each time point to determine the efficacy of the peer mentor program for reducing eating disorder symptoms and quality of life:Clinical demographic and medical history questionnaire: Basic demographic information and a brief medical history will be collected at baseline. At other time points, changes to demographic information and medical history (e.g. new hospital admissions) will be recorded.Eating Disorders Examination Questionnaire (EDE-Q) [29]: The EDE-Q is a 28-item self-report measure of psychological constructs shown to be clinically relevant in individuals with eating disorders. This measure will be used to gather information about eating disorder symptomatology.Depression Anxiety Stress Scale (DASS-21) [30]: The DASS is a 21-item self-report instrument designed to measure the three related negative emotional states of depression, anxiety and tension/stress. Common comorbidities such as depression and anxiety [31] can impact outcomes as well as engagement and adherence and are important targets for intervention as well as being potential adverse outcomes which require monitoring and appropriate action if they reach concerning levels of risk.Brief Disability Questionnaire (BDQ) [32]: The BDQ is a self-report measure of disability in everyday activities and yields two main subscales: physical disability and mental health disability.Assessment of Quality of Life (AQoL) [33]: The AQoL is a self-report instrument that measures health-related quality of life.Feedback questionnaire (not at baseline): General feedback on the program will be sought.

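### The adverse-event criterion names only a completion interview and feedback forms, and is not linked to safety records that the study already collects, so events in people who withdraw are the likeliest to be under-counted

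*Protocol article*

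**What the plan says.** The section Qualitative interviews and feasibility of the protocol article makes tolerance, acceptance and safety part of the feasibility assessment. It names two sources: "identifying any adverse events related to the study through the qualitative interview and the participant feedback questionnaires". The next sentence gives the consequence: "Any serious adverse events will result in the intervention not continuing to an RCT". The same section accepts the study as feasible with 80% of participants completing, provided that the target sample size is reached within 2 years.

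**Timing of the two sources.** The section says that "a broad semi-structured interview schedule will be used on completion of the program", and Program evaluation agrees: "a qualitative interview undertaken upon completion of the program for both mentees and mentors". Quantitative assessments lists the other source as "Feedback questionnaire (not at baseline): General feedback on the program will be sought". With the time points in Program evaluation, that means 3, 6 and 12 months.

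**Withdrawal.** Handling of withdrawals and replacements lets participants leave without giving a reason. It offers them relevant follow-up assessments if they agree, and it seeks a replacement. It describes no exit interview.

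**Other safety information.**
- Mentoring activities: "Mentors will complete an online questionnaire at the conclusion of each mentoring session to document progress and monitor safety considerations". The project coordinator reviews these forms.
- Quantitative assessments: at the later time points, "changes to demographic information and medical history (e.g. new hospital admissions) will be recorded". It also lists the DASS-21 and treats depression and anxiety as possible adverse outcomes to be monitored.
- Risk management and safety: mentees in distress are told to contact the coordinator or research team, and mentors can request a support call through the post-session survey.

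**The concern.** The criterion draws on sources that depend on a person still taking part. Under Risk management and safety, the research team decides after an episode of distress whether a mentee stays in the program, so an adverse experience can itself lead to a missing interview. The Background raises relapse of an active mentor as a risk to be examined, and a mentor who relapses and leaves is in the same position. Replacing people who leave fills the place but does not recover their events.

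Progression to a randomised trial turns on whether any serious adverse event occurred. With about 30 people in each group, very few events may decide the matter. If the stated sources are followed as written, the safety and tolerability picture leans towards those who stayed, and hence towards a favourable reading.

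**Working it through.** The article states no adverse-event rate or count, so there is no figure to reproduce. The check has two parts.

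**1. Which sources can see an event in someone who withdraws**

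| Source | When collected | After withdrawal | Named for the adverse-event criterion |
|---|---|---|---|
| Qualitative interview | Once, on completion | No exit interview described | Yes |
| Feedback questionnaire | 3, 6 and 12 months | Only if the person agrees | Yes |
| Post-session mentor questionnaire | After each of 13 sessions | Stops when sessions stop | No |
| New hospital admissions | 3, 6 and 12 months | Only if the person agrees | No |
| DASS-21 | Baseline, 3, 6 and 12 months | Only if the person agrees | No |
| Distress contacts, support-call requests | Any time or after each session | Not described | No |

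The post-session questionnaires and the contacts are gathered as the program runs, so they can record an event up to the point of leaving. They are the main gain from widening the criterion. Admissions and DASS-21 fall at the same visits as the feedback form and are lost to withdrawal in the same way. They still add something, because they ask about specific health changes and the feedback form is described as general.

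**2. How large the under-count could be (illustration)**

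Inputs from the article: up to 30 mentees (Study design and mentor-mentee matching) and 80% completion counted as feasible. Non-completers tolerated = 0.20 × 30 = 6, leaving 24 completers. Replacements are left out for simplicity.

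Assumptions, not in the article: event risk *pc* in completers, *pw* in withdrawers, and *r*, the share of withdrawers' events that is captured. Events in completers are taken as fully captured.

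Expected events = 24·pc + 6·pw

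Share missed = 6·pw·(1 − r) / (24·pc + 6·pw)

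| pc | pw | Expected events | Missed, r = 0 | Missed, r = 0.5 | Missed, r = 1 |
|---|---|---|---|---|---|
| 5% | 5% | 1.2 + 0.3 = 1.5 | 0.3/1.5 = 20% | 10% | 0 |
| 5% | 10% | 1.2 + 0.6 = 1.8 | 0.6/1.8 = 33% | 17% | 0 |
| 5% | 20% | 1.2 + 1.2 = 2.4 | 1.2/2.4 = 50% | 25% | 0 |
| 5% | 30% | 1.2 + 1.8 = 3.0 | 1.8/3.0 = 60% | 30% | 0 |

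At equal rates the share missed is (6/30)·(1 − r), whatever the rate.

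The progression rule asks only whether any serious event occurred, so the chance of seeing at least one is also relevant. If the assumed rates are read as serious-event risks, with independent participants:

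P(at least one seen) = 1 − (1 − pc)^24 · (1 − r·pw)^6

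With pc = 5% and pw = 20%:
- r = 1: 1 − 0.95^24 × 0.80^6 = 0.92
- r = 0.5: 1 − 0.95^24 × 0.90^6 = 0.85
- r = 0: 1 − 0.95^24 = 0.71

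**The case against.** The strongest reply is that the study is not blind to events in people who leave. Mentors report on safety after every session and the coordinator reviews the reports. Admissions, depression and anxiety are tracked, and distress reaches the research team directly. Feedback forms are also due at 3 months, so someone who leaves later may already have given one, and withdrawers may agree to further assessments. The Discussion commits to assessing adverse effects on mentees and mentors, and a condensed article may leave detailed event recording to the full protocol.

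Most of this stands, and it rules out several stronger readings that a reader might infer:

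- **That events in withdrawers go wholly unrecorded.** The concurrent channels contradict this. The defect is that they are not linked to the criterion.
- **That the bar on a randomised trial applies only to events found by interview or feedback.** The sentence has no source restriction, and nothing says that an event learned another way would be ignored. A safety decision resting on completers alone is a risk under the stated sources, not something the article specifies.
- **That most events would be missed.** Shares of that size need both a much higher event rate in withdrawers and no capture among them. Both are assumptions, and the concurrent channels make zero capture unlikely.
- **That session counts rest on recall at interview.** The article says that these "will also be assessed through the qualitative interviews", but the word *also* matters. Program evaluation tracks attrition from mentors' session records, and the feasibility paragraph uses mentors' participation records.

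Follow-up by agreement after withdrawal is not a fault either, since participants may leave freely.

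The condensation argument does not remove the point. The article does not merely leave the source of adverse-event data to another document: it names the sources for this criterion, and they are the ones that depend most on completion.

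**Conclusion.** The point holds in a limited form. For identifying adverse events and judging tolerability, the protocol article names one interview held at completion and general feedback forms at 3, 6 and 12 months. It does not link the session questionnaires, admissions, DASS-21, distress contacts or support-call requests to that criterion or to the progression rule. Followed as written, this would tend to under-count events in people who withdraw and are replaced, in both groups.

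The direction follows from the text; the size does not. With 6 of 30 mentees withdrawing, the illustration gives 10% to 20% of events missed at equal event rates (half or no capture in withdrawers), and up to 60% at the most unequal rates tried with no capture. All of these rest on assumed rates and capture. This is a worthwhile, inexpensive correction and does not show that the safety assessment would fail.

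**What to change.** Amend the feasibility paragraph in Qualitative interviews and feasibility so that:

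1. Adverse events are counted in every mentee and mentor who started, including those later replaced.
2. The sources are the records already collected: post-session mentor questionnaires, new hospital admissions, DASS-21, distress contacts and support-call requests. The interview and feedback forms become supplementary.
3. The existing interview and feedback form are offered at withdrawal to those who agree, as well as at completion.
4. The report gives events per person started, for mentees and mentors separately, and states how many withdrew.
5. The progression sentence refers to events from all of these sources.

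Reporting exact confidence intervals, or splitting events by completers and withdrawers, is optional: with about six withdrawers it would say little.

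The cost is a wording change, some data extraction, and moving a few interviews to the time of withdrawal. One limit remains: session questionnaires stop when sessions stop, and capture after withdrawal will still depend on the person's agreement. The number of withdrawers without later information should therefore be stated beside the event count.

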### Study AIMS

The aim of this study is to determine the efficacy of a peer mentor program for people who have received eating disorder treatment in a specialist hospital setting or equivalent, in improving eating disorder symptomatology and quality of life, to inform future randomised controlled trials. An additional aim is to determine the feasibility of the study by assessing participants’ capability to complete the mentoring sessions and the program. The study’s feasibility will be measured in terms of having a sufficient number of participants sign up, participate and be retained until the end of the study and also that they tolerate and accept the intervention, that the intervention can be delivered as per protocol and that there are no concerning adverse events related to the study. The current program is a new program that combines peer support principles with documented evidence, balanced against available resource and organisational risk constraints. The program is designed to harness the experience of people who have recovered from eating disorders and combine it with regular de-briefing and supervision. This project aims to ensure eating disorder patients leaving hospital can better sustain their recovery outcomes in the long term. This is the first time such a program has been offered in Victoria, Australia. Thus, the primary aim of the study is to evaluate the effectiveness of the peer mentor program on eating disorder patient outcomes. A secondary, exploratory aim of the program is to evaluate the effects of the program on peer mentors in terms of eating disorder symptomatology and quality of life.

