### Mentor training

Mentors will attend a 3-day training and induction program prior to the program rollout to ensure that mentors are prepared in their role. EDV staff and external trainers deliver different elements of the training dependent on their experience. As the mentors are EDV staff, the training starts with inducting them as employees and going through the procedures and policies outlined for all EDV staff members.

An overview of the Intentional Peer Support (IPS) model is given to all mentors as a framework to base all interactions. This model states that peer support is intentional, in that we come to the relationship with a specific purpose in mind—with the program, this is maintaining recovery. The four core elements of IPS are connection—between the mentor and mentee, holding a worldview and understanding how we have come to know what we know and mutuality—learning and growing together and moving towards identified goals (recorded in the mentee’s Wellness Plans) [27].

Training also covers off the challenging situations mentors might be faced with when supporting their mentee. Information about the program’s aims and objectives are made clear so the mentors know what they are working towards. As there is a high possibility of self-harm and thoughts of suicide, all mentors complete an internationally recognised safeTALK suicide alertness workshop which covers hands-on skills to be able to respond to someone who has the thoughts of suicide [28]. The EDV psychologists also facilitate role-plays with mentors which raise common issues and are discussed.

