## Statistical methods

### Sample size estimation and justification

Thirty mentors and a minimum of 30 mentees will be recruited. This minimum sample size of 60 participants will enable differences to be identified between time points in a pilot evaluation (i.e. 28 participants per group will enable the identification of a moderate effect size with power of 0.8 and alpha of 0.05 for a within-group analysis between baseline and the primary endpoint). Sample size has been determined using the qualitative principle of data saturation, which provides an estimate of sample size based upon the comprehensiveness of the data set to identify all of the issues affecting the population under study. As Fusch and Ness [37] highlight, data saturation is the point when (a) no new insights related to the research aims and objectives are gained from additional interviews or through further analysis and (b) there is sufficient information gathered for the study to be replicated. The proposed participant numbers of 60 or more participants (30 per group) is deemed be sufficient to capture the variance in information that occurs within each participant group. Guest and colleagues [38] argue that data saturation occurs after as few as six interviews, with all information (themes) fully elucidated after 12 interviews. Our prior clinical-based qualitative research [39–41] indicates that this varies considerably based on the population under study but typically occurs after 7 and 14 interviews. Given the variability in the present sample by age, gender and anything else, our planned sample will be sufficient to gather powerful information on our study aims and objectives.

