## Discussion

Eating disorders are disabling and often long-term conditions. The efficacy of available treatments is limited, resulting in high relapse rates and significant morbidity and mortality. The current trial aims to assess the efficacy and feasibility of a peer mentor program (as a supplement to standard treatment) for patients with eating disorders, in terms of improvements in both eating disorder symptomatology and quality of life, as well as relapse rates. A unique aspect of this research is to assess the impact of this program on mentors to identify the positive and/or negative impact that engaging with current eating disorder patients has on someone who has recovered from an eating disorder. This study will assess any adverse effects on mentees or mentors and glean information that will inform refinement of the intervention for a full-scale randomised controlled trial. The findings of this pilot program will inform larger randomised controlled trials assessing the efficacy of peer mentoring for individuals with eating disorders, by providing preliminary data on the need of the program (i.e. participant flow and retention rate, and the magnitude of the outcomes to be clinically significant).

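### The rule that any serious adverse event bars progression to an RCT is not reconciled with the study-related safety criterion stated elsewhere in the protocol

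*Protocol article*

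**What the plan says.** The progression rule closes the feasibility paragraph of the Protocol article, section *Qualitative interviews and feasibility*: "Any serious adverse events will result in the intervention not continuing to an RCT". It carries no qualifier for relatedness, participant group, number of events or period.

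Three other statements bear on the same decision:

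- *Study AIMS* lists among the feasibility conditions "that there are no concerning adverse events related to the study".
- The sentence immediately before the rule describes the safety part of feasibility as "identifying any adverse events related to the study through the qualitative interview and the participant feedback questionnaires".
- *Discussion* says the study will assess adverse effects on mentees or mentors and "glean information that will inform refinement of the intervention for a full-scale randomised controlled trial".

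On the population, mentees are leaving an inpatient unit or moving into or out of a day program. *Mentor training* justifies a suicide-alertness workshop with the words "As there is a high possibility of self-harm and thoughts of suicide". *Quantitative assessments* says that after baseline "changes to demographic information and medical history (e.g. new hospital admissions) will be recorded". *Eligibility criteria* excludes mentees and mentors at serious risk of harm to themselves or others. The design is within-group, with no control arm. On numbers, *Sample size estimation and justification* says "Thirty mentors and a minimum of 30 mentees will be recruited".

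**The concern.** The study exists to inform a later RCT, so the rule that decides whether one follows should have a single meaning. Take one serious event that is plainly unrelated to mentoring. Under *Study AIMS* it does not count. Under the literal progression rule it ends the path to an RCT. The same data can then support opposite decisions, and nothing in the text fixes the choice before results are known.

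The literal rule also answers a different question from the one asked. Mentees have a current eating disorder and have recently needed hospital or day-program care, so some serious events may arise from the illness itself. Without a comparison group, a count of one or more says little about whether mentoring caused harm. *Primary hypotheses* proposes that the program reduces relapse. If a relapse admission counts as serious, a program that did reduce relapse could still fail on a single admission.

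**Working it through.** **Plan's own figure.** There is none to reproduce. The article gives no definition or rate of serious adverse events and no operating characteristic for the rule. Its one design calculation (28 per group for a moderate effect) does not bear on this point.

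**The statements side by side, for one serious event unrelated to the study**

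| Place | Must the event be study-related? | Consequence |
|---|---|---|
| *Study AIMS* | Yes | Event not counted |
| *Qualitative interviews and feasibility*, sentence before the rule | Yes | Event not counted |
| Same section, the rule read literally | Not stated | No RCT |
| *Discussion* | Not stated | Information used to refine the program for a full-scale trial |

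**Inputs for the probability**

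- n = 30 mentees (*Sample size estimation and justification*, where 30 is a minimum; *Study design and mentor-mentee matching* says up to 30).
- p = risk per mentee of at least one serious event over the counting period. The documents do not give it; 1% to 10% is assumed here.
- Participants are taken as independent.

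**Formula.** P(rule fires) = 1 − (1 − p)^n

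| Assumed p | Calculation | P(at least one among 30) |
|---|---|---|
| 1% | 1 − 0.99^30 | 0.260 |
| 2% | 1 − 0.98^30 | 0.455 |
| 5% | 1 − 0.95^30 | 0.785 |
| 10% | 1 − 0.90^30 | 0.958 |

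**Inverse.** The risk at which the rule fires with probability P is 1 − (1 − P)^(1/30). This gives 2.3% for P = 0.50, 7.4% for P = 0.90 and 9.5% for P = 0.95.

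**Mentor events.** Mentors must have been in recovery for at least 2 years, so they should not be given the mentees' risk. With an assumed 1% for 30 mentors and 5% for 30 mentees, 1 − 0.95^30 × 0.99^30 = 0.841. With 10% for mentees, 1 − 0.90^30 × 0.99^30 = 0.969. Mentors add to the probability, but mentee risk dominates it.

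**Effect of requiring relatedness.** The related share of events is also an assumption. At an overall mentee risk of 10%:

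- if one tenth of events are related, p = 1% and the probability falls from 0.958 to 0.260;
- if half are related, p = 5% and it falls only to 0.785.

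The qualifier can change the decision materially. It does not remove the general property that a zero-event rule fires more often as more people are enrolled.

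**The case against.** The strongest reply is that the rule follows directly on a sentence limited to study-related events, so it may simply mean the serious subset of those. On that reading it agrees with *Study AIMS*. This is a fair reading. For that reason the point is an unreconciled inconsistency, and a reader who inferred a strict contradiction would go further than the text allows. But the rule opens with an unrestricted subject and is the only one of these sentences that states a decision, so the literal reading remains open.

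A reader might also infer that the rule makes refusal of an RCT close to automatic. The documents do not support that without conditions. They give no rate. Recording new admissions is not the same as expecting them, and the remark about self-harm explains a training module and does not estimate serious events. People at serious risk of harm are excluded, and mentees must be under the care of a GP and a psychologist. Detection largely through interviews and feedback forms may also lower the recorded count. At 1% to 2% the rule fires in 26% to 45% of such studies.

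It can further be said that zero tolerance for serious events is a legitimate cautious choice in a vulnerable group, and that definitions and causality assessment usually sit in the full protocol. Both stand. Missing definitions are not the complaint here. The complaint is that the article states the rule outright and states it differently elsewhere. If strictness is intended, *Study AIMS* and *Discussion* should say so.

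**Conclusion.** The point holds as an inconsistency in a stated decision rule. Read literally, one unrelated serious event in a mentee or mentor would bar an RCT; read with *Study AIMS*, it would not. The uncontrolled design gives no way to attribute the event.

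The size is conditional. Among 30 mentees the chance that the literal rule fires runs from 26% at an assumed 1% risk to 96% at 10%, passing 90% at about 7.4%. The upper part of that range is plausible if hospital readmission is classed as serious, but that classification is an assumption, as are the rates and independence between participants. No estimate, test or sample size in the plan is affected. What is at stake is the validity of the progression decision.

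**What to change.** Reconcile *Study AIMS*, *Qualitative interviews and feasibility* and *Discussion* into one research-progression criterion, stated once. It should say:

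- whether an event must be related to the study and, if so, that relatedness is classified before outcome results are seen;
- whether mentor events count as well as mentee events;
- the counting window (the 6-month program, or through the 12-month follow-up).

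Report all serious adverse events, related or not, as the number of people affected in each group with exact 95% confidence intervals. If the unqualified rule is what the sponsor intends, say so explicitly, align the other two sections with it, and state its probability of firing across the assumed rates above.

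The cost is a sentence or two of amendment. If relatedness is used, a judgement must be recorded for each event. In an open, uncontrolled program that judgement is subjective, which is why its timing should be fixed in advance. The handling of individual participants under *Risk management and safety* is not affected.
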